### Procedure for unblinding if needed {17b}

Non-applicable since the HOPExt is an open-label trial.

## Data collection and management

### Plans for assessment and collection of outcomes {18a}

Investigators are responsible for the assessment and collection of outcomes, baseline, and other trial data. Data will be entered in the electronic case report form by delegated team members and will be monitored by trained clinical research assistants (CRA) designated by the sponsor. The digitalized version of the case report form is provided in Supplemental Material 2 (French version). CRA mandated by the sponsor will ensure the proper conduct of the study, collection of written data, their documentation, recording, and reporting in conformity with the Good Clinical Practices.

The investigator and the members of their team will accept to make themselves available during the quality control visits performed at regular intervals by the CRA. During these visits, the following elements may be reviewed:Informed consentRespect of the study protocol and the procedures defined thereinQuality of the data recorded in the case report form: accuracy, missing data, consistency of the data with the source documentsManagement of the experimental treatments/strategiesDeclaration of serious adverse events

All visits will be the subject of a written monitoring report addressed to the investigator of the site visited and to the study coordinating structure.

### Plans to promote participant retention and complete follow-up {18b}

All follow-up visits of the HOPExt trial are part of the routine clinical follow-up after liver transplantation. No lost-to-follow-up are thus expected in this study.

### Data management {19}

Patient data needed for the study will be collected in an e-CRF. This e-CRF, developed via the Ennov Clinical software, will be specific to the study.

The patient code (see the paragraph “Confidentiality {27}”) will be the only information on the e-CRF which will link the data to the patient.

The e-CRF will only include the data needed to analyze the efficacy and safety of patients and for publication (information required by the protocol). Other data relating to the patient and necessary for their follow-up outside the study will be collected in their medical file. An explanation will be provided for each missing data.

At the end of the study, a paper print will be requested, which must be authenticated (dated and signed) by the investigator. A copy of the authenticated document for the sponsor must be archived by the investigator.

### Confidentiality {27}

In accordance with provisions concerning the confidentiality of data to which persons responsible for the quality control of a study involving human individuals have access (article L.1121–3 of the public health code), and in accordance with the provisions regarding the confidentiality of information relating, in particular, to the trial, the persons who participate, and the results obtained (article R.5121–13 of the public health code), the persons having direct access to the data will take all necessary precautions to ensure the confidentiality of the information related to the trials, to the persons participating and, in particular, with regard to their identity as well as the results obtained.

These persons, as with the investigators themselves, are subject to professional confidentiality (in accordance with the conditions defined by articles 226–13 and 226–14 of the penal code).

During the research involving human individuals or at its end, the data collected on the persons participating and sent to the sponsor by the investigators (or any other specialists) will be made anonymous.

Under no circumstances should the names or the addresses of persons concerned appear.

Only the first letter of the subjects’ surname and the first letter of their first name shall be recorded, accompanied by a coded number specific to the study indicating the center number and the inclusion order of the subject.

The sponsor will ensure that each person participating in the research has given their written agreement granting access to the individual data that concerns them and strictly necessary for the quality control of the study.

### Plans for collection, laboratory evaluation, and storage of biological specimens for genetic or molecular analysis in this trial/future use {33}

A metabolic assessment of the liver biopsies will be performed. Using pre-defined criteria (lactate > 8.4 and/or phosphocholine > 0.646), the level of MELG (metabolically extended liver grafts) both before and after machine perfusion will be compared within the experimental group. The level of MELG in both groups (experimental and control) will also be correlated with the risk of graft dysfunction or graft loss at 1 year.

In the control group, a biopsy of the liver graft will be taken at the beginning of the back-table preparation. Another biopsy will be taken after liver graft reperfusion in the recipient (routine practice).

In the experimental group, a biopsy of the liver graft will be taken at the beginning of the back-table preparation. Another biopsy will be taken at the end of the HOPE perfusion, and a third biopsy will be taken after liver graft reperfusion in the recipient (routine practice).

Immediately after collection (maximum 5 min after collection), the biopsy will be placed in 2-ml microvials to be either frozen in liquid nitrogen or put in allprotect®. They will then be stored at − 80 °C in each center.

Biopsies, realized at the beginning of the black-table for both groups and at the end of the HOPE perfusion for the experimental group, will be centralized at the end of the study at I-Cube laboratory (UMR 7357—Pr [name] at l) in Strasbourg, France, for analysis. Approximately 30 metabolites of interest will be analyzed by spectrometry (Brucker Avance III 500 spectrometer). A histological study of the samples analyzed by spectroscopy will also be performed. The samples will be destroyed at the end of the analysis.

Since those biopsies will be performed on a liver graft from a deceased donor, an authorization from the Agence de la Biomédecine (ABM) was required and has been obtained.

## Statistical methods

### Statistical methods for primary and secondary outcomes {20a}

#### Analysis sets

##### Full analysis set (FAS)

All randomized and transplanted subjects will be considered for the FAS analysis (modified intention-to-treat analysis). This population will be used for efficacy analyses.

Patients randomized in the perfusion group (HOPE) and for whom perfusion cannot be initiated for any reason will be analyzed in the intention-to-treat analysis and considered in the group in which they were randomized. This population will be used for efficacy and feasibility analyses.

##### Per protocol (PP)

This population includes all subjects evaluable in FAS who ended the study without any major protocol deviation, analyzed in the group to which they are allocated by randomization. Major deviations will be defined individually during a data review/blind review meeting. Major deviations detected will be, for example:Non-respect of protocol timeframe for planned visitsRandomization errors

This population will be used for efficacy analyses.

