## Introduction

### Background and rationale {6a}

Ischemia–reperfusion (I/R) injury is universal in organ transplantation and results in microcirculatory and hepatocellular damage [1]. After liver transplantation, I/R leads to various degrees of graft dysfunction. Liver transplantation encompasses two forms of liver ischemia, namely cold and rewarming ischemia, both inducing hepatocellular injury. Cold ischemia occurs during organ retrieval, when the liver is cooled, perfused and then stored in a cold preservation solution. Rewarming ischemia is encountered during back-table graft preparation and also at the implementation stage while performing the vascular anastomoses before reperfusion [2]. Despite this fact, the preservation method for organ transplantation has been left unchanged for many years and simple static cold storage still remains the gold standard worldwide.

Given the scarce donor supply, an increasing number of so-called marginal or extended criteria donor (ECD) organs are used for liver transplantation, grafts which were previously rarely considered [3]. While there is no international consensus on the definition, ECD criteria include donor’s age over 65 years, donors in intensive care therapy for more than 7 days, obesity, fatty liver, prolonged cold ischemia time for over 12 h, and elevated liver enzymes or high natremia at any time in the donor. According to EuroTransplant and the French organ procurement organization (OPO) “Agence de la Biomédecine”, 40 to 50% of liver grafts are provided from ECD donors in Europe and in France, with the rate increasing over recent years (2016 report by the “Agence de la biomédecine”). These ECD liver grafts are however known to be associated with a higher rate of early allograft dysfunction (EAD) and primary non-function (PNF) because of a greater vulnerability to I/R injury. Although most authors agree that the graft function finally recovers, EAD is associated, in turn, with increased recipient susceptibility to sepsis [4], longer intensive care unit (ICU) and hospital stays [5–7], graft loss [8], and greater morbidity and mortality [9, 10].

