### Objectives {7}

#### Primary objective

To assess the efficacy of HOPE, used before the transplantation of ECD liver grafts from brain-dead donors, in reducing postoperative early allograft dysfunction (EAD) within the first 7 postoperative days (POD) compared to simple cold static storage.

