##### Safety population (SAF)

This dataset includes all transplanted subjects for whom at least one follow-up safety data is available. This population will be used for safety analyses.

The primary population of interest will be the FAS.

Descriptive summary statistics for continuous variables will include the number of observations (*n*), mean, standard deviation (SD), median, minimum (min), maximum (max), and 25th and 75th percentiles (IQR). Descriptive summary statistics for categorical data will include frequency counts and percentages *N* (%). Percentage calculations will be based on the number of patients for whom there are no missing data.

The primary endpoint will be expressed as the total number of cases in each group and in percentages, with a 95% confidence interval. The categorical variables of the secondary endpoints will also be expressed as the total number of cases in each group and in percentages with a 95% confidence interval.

Categorical variables will be compared between the two study arms using the chi-squared test or the Fisher’s exact test, as appropriate. The continuous variables of the secondary endpoints will be compared using the Mann–Whitney *U* test.

In order to take into account the potential effects of confounders on the primary endpoint, univariate and multivariate logistic regressions will be performed.

90-day morbidity and mortality will be studied using a Kaplan–Meier analysis and comparison between groups will be performed using the log-rank test.

A *p*-value < 0.05 will be considered as statistically significant.

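### The per-protocol set for the day-7 EAD endpoint is defined by conduct over the whole 12-month study, so events after the outcome is known can remove patients from that supportive comparison

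*Protocol article*

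**What the plan says.** All references are to the Protocol article.

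- **Per protocol (PP).** "This population includes all subjects evaluable in FAS who ended the study without any major protocol deviation". Patients are analysed in the arm to which they were randomized. On deviations: "Major deviations will be defined individually during a data review/blind review meeting". Two examples follow: planned visits outside the protocol timeframe, and randomization errors. On use: "This population will be used for efficacy analyses". No endpoint is separated out.
- **Primary objective {7}.** HOPE is assessed for its effect "in reducing postoperative early allograft dysfunction (EAD) within the first 7 postoperative days". The Primary endpoint section {12} fixes every EAD criterion at or before POD 7.
- **Participant timeline {13} and Table 1.** Follow-up lasts 12 months. After discharge, visits are planned at months 3, 6, 9 and 12, each with a window of ±30 days.
- **Background and rationale {6a}.** "EAD is associated, in turn, with increased recipient susceptibility to sepsis". The same sentence goes on to longer stays, graft loss, and greater morbidity and mortality. It reports associations and gives no rates.
- **Full analysis set and primary population {20a}.** "All randomized and transplanted subjects will be considered for the FAS analysis (modified intention-to-treat analysis"). Then: "The primary population of interest will be the FAS".

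**The concern.** A PP analysis should show whether the main result holds among patients treated and assessed as planned. For an outcome complete on POD 7, nothing after POD 7 bears on that question. The definition nevertheless looks at conduct up to month 12. A patient with known EAD status could leave the EAD comparison because of a late month-9 visit. If ending the study means completing it, a withdrawal at month 6 or a death at month 4 would have the same effect.

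This would be selection on events after the outcome. If patients with EAD have more later trouble, as the background suggests, they would be removed more often. Both EAD rates would then be understated and the absolute difference would shrink. The primary endpoint is expressed as a difference in proportions, so the shrinkage falls on the scale on which the trial reports its result. A gap between PP and FAS would then be harder to read, because part of it could come from who was removed rather than from how the graft was preserved.

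**Working it through.** **1. Reproduce the planned size.** Inputs from Sample size {14}: 30% v 15%, two-sided alpha 0.05, power 0.80, and the R two-proportion power function, which uses the arcsine effect size.

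- h = 2·asin(√0.30) − 2·asin(√0.15) = 0.3639
- n = 2·[(1.960 + 0.842)/0.3639]² = 118.6, so 119 per group, as stated
- Dropout: 119/0.9 = 132.2, so 133 per group, as stated

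**2. Choose the base for the illustration.** The figure of 119 is already net of the plan's 10% allowance for dropout and premature termination. Taking PP losses off 119 would charge for dropout twice, so the base is 133 per group with no other loss. Power there is Φ(0.3639·√(133/2) − 1.960) = 84%.

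**3. Model the removal.** Let a be the share of EAD patients removed by events after POD 7 and b the share of non-EAD patients, the same in both arms. The documents give neither, so both are assumed. For a true rate p:

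- fraction kept: k = p(1−a) + (1−p)(1−b)
- observed PP rate: p′ = p(1−a)/k
- power: Φ(h′·√[n₁n₂/(n₁+n₂)] − 1.960), with h′ from the two PP rates and nᵢ = 133·kᵢ

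Worked case, a = 25% and b = 8%:

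- Control: k = 0.225 + 0.644 = 0.869; p′ = 0.225/0.869 = 25.9%; n = 115.6
- HOPE: k = 0.1125 + 0.782 = 0.8945; p′ = 0.1125/0.8945 = 12.6%; n = 119.0

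| a / b (assumed) | Control v HOPE | Difference (points) | n per arm | Power | Odds ratio |
|---|---|---|---|---|---|
| 0 / 0 | 30.0% v 15.0% | 15.0 | 133 v 133 | 84% | 0.41 |
| 20% / 10% | 27.6% v 13.6% | 14.0 | 116 v 118 | 77% | 0.41 |
| 25% / 8% | 25.9% v 12.6% | 13.3 | 116 v 119 | 75% | 0.41 |
| 30% / 10% | 25.0% v 12.1% | 12.9 | 112 v 116 | 72% | 0.41 |

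**4. Separate the two causes of lost power.** In the 25%/8% case, keeping the reduced numbers but leaving the rates at 30% v 15% gives 80%. About half of the fall from 84% to 75% is plain loss of patients, and the rest is outcome-dependent removal.

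**5. Check the odds ratio.** The odds in each arm are multiplied by the same factor, (1−a)/(1−b), which cancels. The odds ratio stays at (0.15/0.85)/(0.30/0.70) = 0.41, and a null effect stays null. Biasing it needs removal that differs by arm. For example, with a true 30% in both arms and 5% of non-EAD patients removed in each, removing 30% of EAD patients in one arm and 10% in the other gives 24.0% v 28.9%. The odds ratio is then (0.240/0.760)/(0.289/0.711) = 0.78 where the truth is 1. Nothing in the documents says that removal would differ in this way.

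**The case against.** The case on the other side is substantial.

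- **PP is not the primary population.** The FAS carries the main comparison and has no condition on later conduct. The sample size section plans no power for PP. This stands in full.
- **Late visits are an example, not an automatic exclusion.** Deviations are judged one by one at a blind review, which could rule a late month-9 visit irrelevant to a POD 7 outcome. This stands, and it is why the point says could. Blinding to arm does not, however, stop exclusions from following the consequences of EAD, and the paragraph gives the reviewers no instruction to judge by endpoint.
- **Death and withdrawal are not listed as deviations.** The wording may only mean that no major deviation occurred by the end of participation. The completion reading is plausible, because sections {11b} and {14} speak of patients who end the study early, but it is not the only one. The ambiguity itself needs removing.
- **Little loss is expected.** Section {18b} expects none to follow-up, and the later windows are wide. That does not cover deaths or late visits, and section {14} itself allows 10% for dropout and premature termination.
- **The detail may sit in the full protocol or SAP.** Endpoint-specific criteria often do. Here, though, the article states a general rule and applies it to efficacy without distinction.

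A reader might infer that EAD patients will certainly be removed most, or that the PP result would be uninterpretable. The documents support neither. The background reports associations without rates and says nothing on visit punctuality or withdrawal by EAD status. With equal removal in both arms, the odds ratio and the null are preserved.

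**Conclusion.** The point holds for the supportive PP analysis only. As worded, the PP definition allows events after POD 7 to decide who enters a comparison of an outcome already observed. For late visits this follows from the deviation example, subject to the review meeting. For later deaths and withdrawals it depends on reading the phrase about ending the study as completion.

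The size cannot be derived from the documents. Under the assumed removal rates, equal in both arms, the absolute difference falls from 15.0 points to between 12.9 and 14.0, and PP power falls from 84% to about 72-77%. The odds ratio is unchanged at 0.41. These figures also assume that PP exclusions are the only loss from 133 per group. The consequence is modest attenuation on the absolute scale and a PP result that is harder to set beside the FAS result. The primary FAS analysis and its planned power are untouched.

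**What to change.** In the PP paragraph, make the definition specific to the endpoint.

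1. For the EAD analysis, define PP only by deviations up to POD 7: eligibility, correct randomization, allocated preservation received, and POD 1-7 assessments.
2. Replace the condition about ending the study, which can be read as 12-month completion.
3. State that deaths, withdrawals and visit-timing deviations after POD 7 do not exclude a patient from the EAD PP analysis.
4. Apply later visit windows only to the endpoints measured at those visits.

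The blind review meeting can stay, working from these rules. The cost is one paragraph of analysis wording, with no new data and no change to the primary analysis or sample size. It should be settled before the review meeting takes place.

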##### Safety population (SAF)

This dataset includes all transplanted subjects for whom at least one follow-up safety data is available. This population will be used for safety analyses.

The primary population of interest will be the FAS.

Descriptive summary statistics for continuous variables will include the number of observations (*n*), mean, standard deviation (SD), median, minimum (min), maximum (max), and 25th and 75th percentiles (IQR). Descriptive summary statistics for categorical data will include frequency counts and percentages *N* (%). Percentage calculations will be based on the number of patients for whom there are no missing data.

The primary endpoint will be expressed as the total number of cases in each group and in percentages, with a 95% confidence interval. The categorical variables of the secondary endpoints will also be expressed as the total number of cases in each group and in percentages with a 95% confidence interval.

Categorical variables will be compared between the two study arms using the chi-squared test or the Fisher’s exact test, as appropriate. The continuous variables of the secondary endpoints will be compared using the Mann–Whitney *U* test.

In order to take into account the potential effects of confounders on the primary endpoint, univariate and multivariate logistic regressions will be performed.

90-day morbidity and mortality will be studied using a Kaplan–Meier analysis and comparison between groups will be performed using the log-rank test.

A *p*-value < 0.05 will be considered as statistically significant.

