## Methods: participants, interventions, and outcomes

### Study setting {9}

The study is conducted in eight transplantation centers located in University hospitals scattered throughout France. The list of participating centers is presented in Supplementary Material 1.

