### Outcomes {12}

#### Primary endpoint

Difference between the two treatment arms in the proportion of patients with early allograft dysfunction (EAD). EAD (according to Olthoff et al. [7]) is defined by the presence of at least one of the following criteria:Bilirubin level > 10 mg/dL (i.e., 171 μmol/L) on postoperative day (POD) 7INR > 1.6 on POD 7AST or ALT level > 2000 IU/L within the first 7 PODs

Primary non-function (PNF) of the graft is the very last stage of any EAD and is defined by the presence of at least one of the following criteria:Graft loss within the first 7 PODsPatient’s death within the first 7 PODs

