## Assignment of interventions: allocation

### Sequence generation {16a}

Randomization will be performed after the allocation of the graft or after the harvesting team has macroscopically assessed the graft, according to the center practice.

It will be stratified by center and MELD score at the time of transplantation, with a cut-off of 30 (MELD < 30 versus MELD ≥ 30).

The randomization process will be centralized and carried out via Ennov Clinical software. The randomization list will be drawn up by the methodologist/biostatistician of the Clinical Research Center at the Croix-Rousse University hospital, Lyon, France.

The randomization list will be kept for 25 years in a tamper-proof envelope with the mandatory information (signature of the person in charge of the list, date and version number, complete title, and code of the research protocol). This list will also be sent to the Clinical Research Center data manager for implementation in the Ennov Clinical software.

The investigator or a person designated by the principal investigator will randomize patients via the Ennov Clinical software. Only authorized persons will be able to perform the randomization. A confirmation email will be sent to the person who performed the randomization after each randomization, to the investigator associated with the patient, and to the management center.

In case of cancellation of the transplant for any reasons, the data manager will cancel the randomization. The patient will remain included in the study for randomization in one of the study arms.

The whole process (randomization, modifications, etc.) will be recorded in the audit trail of the study, which will be integrated in the clinical data management system (CDMS). This audit trail will be transmitted at the end of the study to be archived with all the study documents.

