### Concealment mechanism {16b}

Allocation concealment will be ensured via a central web-based system (Ennov Clinical® 7.5.720). The procedure to which a patient will be allocated will be disclosed only after enrolment in the study. Moreover, since a blocked randomization is used, the block size is not disclosed in the protocol making it impossible to predict the randomization sequence.

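### The EAD comparison ignores the randomization strata and, as worded, gives no interval for the between-arm difference: a valid plan that can be improved at no cost

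*Protocol article*

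**What the plan says.** The endpoint is a contrast. Under Primary endpoint, the Protocol article defines it as "Difference between the two treatment arms in the proportion of patients with early allograft dysfunction (EAD").

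The randomization is restricted. Sequence generation {16a} states: "It will be stratified by center and MELD score at the time of transplantation, with a cut-off of 30". Concealment mechanism {16b} adds: "since a blocked randomization is used, the block size is not disclosed in the protocol". Study setting {9} gives eight centers, so there are up to 8 × 2 = 16 strata.

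The analysis does not use the strata. In Statistical methods for primary and secondary outcomes {20a}, in the text below the Safety population heading, the comparison is: "Categorical variables will be compared between the two study arms using the chi-squared test", with Fisher's exact test as the alternative. The presentation is: "The primary endpoint will be expressed as the total number of cases in each group and in percentages", followed by a 95% confidence interval. No risk difference, risk ratio or odds ratio with an interval is named. For adjustment, the same section says that "univariate and multivariate logistic regressions will be performed" to allow for confounders. The covariates are not named, center and MELD are not mentioned, and the regression is not designated the primary analysis.

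**The concern.** There are two mismatches between the design and the analysis.

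1. **Strata used for allocation but not in the test.** Blocking within strata balances the arms on center and MELD. If these factors predict EAD, the true variance of the between-arm difference is smaller than the chi-squared test assumes. The test then rejects too rarely under the null hypothesis and gives up some power. A link with MELD is plausible from the document alone: the Screening visit section lists INR and bilirubin among the inputs of MELD, and two of the EAD criteria are bilirubin and INR on postoperative day 7.

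2. **Intervals per arm for an endpoint that is a difference.** Two separate intervals do not tell the reader how precisely the effect is estimated. They also do not allow a direct comparison with the 15-point reduction that the trial was sized to detect.

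At stake are a modest amount of power in a trial sized at 80%, and an explicit interval for the quantity of interest.

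**Working it through.** **Step 1. Reproduce the plan's own figure.** Inputs from Sample size {14}: 30% versus 15%, two-sided alpha 0.05, power 0.80, the two-proportion function of the R package pwr (arcsine method).

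- h = 2·asin(√0.30) − 2·asin(√0.15) = 0.3639
- n = 2 × ((1.960 + 0.842)/0.3639)² = 118.6, rounded up to 119 per group
- 119/0.90 = 132.2, rounded up to 133 per group

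Both stated figures reproduce. The sample size belongs to an unstratified comparison, so it agrees with the planned test. The normal-approximation power of the uncorrected chi-squared test at 119 per arm is 79.5%.

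**Step 2. Unstratified chi-squared against the Cochran-Mantel-Haenszel (CMH) test.** Trials of 238 patients in 8 centers × 2 MELD strata were simulated with 1:1 permuted blocks, 30% versus 15% for power and equal rates for type I error. The document does not give the following, so they are assumptions: 25% of patients with MELD ≥30, block size 4, the MELD odds ratio, and the SD of center effects on the log-odds scale. With 12,000 trials per scenario:

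| Assumed MELD odds ratio, center SD | Type I error, chi-squared / CMH | Power, chi-squared / CMH | Power gain (points) |
|---|---|---|---|
| 1, 0 (not prognostic) | 0.052 / 0.052 | 0.804 / 0.799 | −0.5 |
| 2, 0.4 | 0.045 / 0.050 | 0.805 / 0.813 | 0.8 |
| 3, 0.6 | 0.037 / 0.046 | 0.809 / 0.828 | 1.9 |
| 4, 0.8 | 0.034 / 0.051 | 0.812 / 0.851 | 3.9 |

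A separate run of 40,000 trials per scenario agrees. With odds ratio 2 and SD 0.5, type I error is 4.2% against 4.9% and power 80.5% against 81.9%. With odds ratio 2 and SD 0.8, type I error is 3.7% against 5.0% and power 81.2% against 83.8%.

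With weaker effects the gain vanishes. At odds ratio 1.5 and SD 0.3, with equal or unequal centers and 10% or 25% of patients above the cut-off, power was 0.798–0.802 for chi-squared and 0.796–0.799 for CMH.

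**Step 3. What per-arm intervals hide.** At the planned rates with 119 per arm, the difference has a 95% CI of 0.15 ± 1.96 × √(0.30×0.70/119 + 0.15×0.85/119) = 0.15 ± 0.104, that is 4.6 to 25.4 points. The plan would show instead 21.8–38.2% and 8.6–21.4%.

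Take a smaller observed effect, 36/119 (30.3%) against 22/119 (18.5%):

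- Difference: 0.3025 − 0.1849 = 0.118
- Standard error: √(0.3025×0.6975/119 + 0.1849×0.8151/119) = 0.0551
- 95% CI: 0.118 ± 1.96 × 0.0551, that is 1.0 to 22.6 points; uncorrected chi-squared p = 0.035
- Per-arm intervals: 22.0–38.5% and 11.5–25.5%, which overlap between 22.0% and 25.5%

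A reader given only the two per-arm intervals sees overlap. The interval for the difference excludes zero but reaches down to 1 point.

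**The case against.** The strongest reply is that nothing is broken.

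- **Power.** A reader might infer that the trial is underpowered. It is not: the sample size was computed for an unstratified comparison, and the chi-squared test had simulated power of about 0.80–0.81 in every scenario of the table. Stratifying would add a bonus and repair no shortfall. This stands.
- **Type I error.** A reader might infer that the 5% level is not protected. The departure is in the safe direction, so a significant result remains valid. This stands.
- **Prognostic strength.** The document gives no association between MELD and EAD and no variation in EAD between centers. MELD is measured before transplantation, the EAD criteria with the new liver, and the AST/ALT criterion shares nothing with MELD. The gain may be close to nil. This stands, and it is why a range is shown.
- **The regression.** A reader might take it for covariate selection by p-value. The text states no selection rule, so that reading is unsupported. Center and MELD are not excluded either, and a covariate list may properly sit in the analysis plan or full protocol. It remains that the regression is not made primary and does not mention the stratifiers.
- **The interval.** A reader might infer that no interval for the effect will ever be reported. That goes too far: the endpoint is itself a difference, the word "only" does not appear, and logistic regression ordinarily yields an odds ratio with an interval. Per arm is still the natural reading, and the text should not leave this open.

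A separate analysis plan may exist, but the Protocol article itself names the test and the presentation, so the comment applies to what it fixes.

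**Conclusion.** The point holds as a free improvement, not as an error that threatens the trial's conclusion. The planned unstratified test is valid and roughly meets the stated 80% power. If center and MELD predict EAD with the assumed strength (odds ratios 2–4, center SD 0.4–0.8), its type I error is about 3.4–4.5% and it forgoes about 1–4 points of power. If they do not, the two tests differ by less than 1 point. These figures rest on the assumed share of 25% with MELD ≥30, blocks of 4 and the assumed stratum effects, none of which the document gives.

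The case for an explicit interval for the difference needs no such assumption. It follows from the endpoint definition and from the arithmetic in the 36/119 versus 22/119 example.

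**What to change.** State the following before the treatment codes are revealed to the analyst:

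- Base the primary analysis of EAD on a method that accounts for the randomization strata, for example a Cochran-Mantel-Haenszel test by center and MELD stratum (<30, ≥30). Other analyses that account for the strata are equally acceptable.
- Report the stratified risk difference with its 95% CI, next to the per-arm counts and percentages already planned.
- Keep the unadjusted chi-squared test as a sensitivity analysis.
- Include the stratification factors in the planned logistic model.

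The cost is wording only. Center and MELD at transplantation are already recorded for randomization, and neither the sample size nor the data collection changes. If the strata turn out uninformative, the expected loss of power is under 1 point.
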